#### Sex as a biological variable

We will examine each of secondary hypotheses (2a, 2b, 3a, and 3b) with respect to difference by sex. In particular, the respective analysis method will be used and a sex by treatment interaction to test whether there are differential treatment effects by sex.

### Interim analyses {21b}

If study recruitment fails to meet quotas and the original target sample size appears unlikely to be achieved, investigators will propose an updated target sample size and conduct a futility analysis. Conditional power will be calculated based on the treatment effect size observed in the current data and “information fraction” consistent with the updated target sample size. This analysis indicates the likelihood of finding a significant effect if trends in the current data continue and the updated sample size target is met. If conditional power under the updated sample size fails to meet a pre-specified threshold of 0.5, the stopping rule will be considered satisfied. If, on the other hand, conditional power is high, the trial is likely to meet its primary outcome even with the reduced sample size. The DSMB will use this information to guide its recommendation to continue or discontinue the trial.

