### Sample size {14}

Assuming *α* = 0.05, power=.80, and *N*=240, we computed the minimum detectable odds ratio (*OR*) and absolute proportion difference (*pdiff*), assuming the three post-intervention time points are part of the contrast. We varied the within-subject correlation *ρ* from 0.10 to 0.80. Power for a binomial is lowest when the base-rate (control group) probability (*P*_0_) is near 50%. Minimum detectable effects are 15% absolute difference in proportions and depend on the base-rate of suppression in the standard of care (*P*_0_) and the level of autocorrelation. This size of effect falls within published cutoffs of small to medium effect sizes [39].

Power analyses were generated using the generalized estimating equations-based two-group repeated proportion module in NCSS PASS 2020 to compute minimum detectable effect sizes for the proposed primary analysis. The study will begin with 240 participants evenly assigned to the intervention and control groups (80 per city). Our primary analysis strategy will assume any participant dropping out of the study has not achieved the outcome.

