## Assignment of interventions: blinding

### Who will be blinded {17a}

This clinical trial is unblinded. For a robust and unbiased approach, our randomization procedure is strong with central control external to the three sites. All data analysis strategies are pre-specified and the finalized data analysis plan will be confirmed prior to data lock. The data analysis will not be blinded since [name] and [name] are study investigators and performing the analysis. [name] and [name] will, however, be blinded to treatment assignment in conducting their analysis until results are finalized.

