#### Primary inferential analyses to address primary aim (Hypothesis 1)

We hypothesize that, for those randomized to the *THR* arm, the odds of our primary outcome, HIV viral suppression, will be higher than for those randomized to off-site linkage to HIV care (control) arm (Hypothesis 1). Generalized estimating equations (GEE) [54] will be used to perform the proposed primary analysis, which is a planned time-averaged comparison of post baseline measurements of HIV viral suppression across the *THR* and control groups to test primary Hypothesis 1. Alpha will be set at 0.05 for this planned comparison. Planned post hoc comparisons will examine the difference between conditions at each of the three assessment times.

Though GEE estimates are consistent even if the correlation structure is mis-specified, GEE’s statistical efficiency improves as the working correlation structure more closely approximates the actual correlation structure, so various correlation structures suitable for the study’s design will be considered (e.g., exchangeable, autocorrelated, *m*-dependent, unstructured). The QIC statistic will be used to select the final correlation structure. Recruitment city (Miami vs. Tampa or Ft. Lauderdale) will be included in all models as required by the stratified randomized design to obtain unbiased results. Robust standard errors will be used to obtain correct inferences even if the chosen correlation structure remains slightly mis-specified. All analyses will include outlier and influential case screening via computation of GEE-based residual analysis, including leverage, DFBeta, and Cook’s D statistics. If outliers are found, results will be reported with and without outliers included.

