#### Monitoring of safety data by the DSMB

Safety information will be reported to the DSMB in an unblinded manner. A statistical penalty will not be assessed for the ongoing unblinded review of safety by the committee. Unblinded data will not be released to site investigators unless necessary for safety reasons. If requested by the DSMB, other unblinded data will be reported to investigators. It is necessary for the purpose of monitoring the safety of the study that the committee review not only adverse events (AEs) and SAEs, but also other data that may reflect differences in safety between groups, including retention rates and reasons for dropout.

Expedited review by the medical monitor will occur for all events meeting the FDA definition of SAE. SAEs include any event that a study investigator or the DSMB judges to impose a significant hazard, contraindication, or side effect. The following SAEs will be reported in REDCap within 24 h: deaths, hospitalizations, fatal and non-fatal drug overdose, and psychiatric hospitalizations. For purposes of this study, all SAEs will be required to be reported to the DSMB, regardless of any judgment of their relatedness to the study, at regular meetings. If the medical monitor deems the SAE to be study related, it will be immediately reported (within 24 h) to the DSMB via email, to the IRB if the risk to subjects was previously not known (i.e., consent/protocol change necessary), and to the NIDA Program Official by email. Unfortunately, SAEs such as fatal and non-fatal overdose are expected due to the study population. All relevant information about the event and its outcome, study condition, concomitant medications, the subject’s medical history and current conditions, and laboratory data will be reported. Information will be reviewed and a determination made of whether there was any possible relevance to the study interventions. Reporting to the IRB will be completed according to guidelines. Reporting to the NIH will be made according to their respective regulations governing SAEs. SAE reporting to the DSMB will occur at the regular meetings, unless deemed significant and related to the study.

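### The investigators both propose the reduced sample size and run the effect-based futility analysis, with nothing separating the trial team from the interim comparative result

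*Protocol article*

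**What the plan says.** Interim analyses {21b} applies when recruitment misses its quotas and the original target looks out of reach. In that case "investigators will propose an updated target sample size and conduct a futility analysis". Conditional power is computed from the effect seen so far and the information fraction implied by the updated target. A value below 0.5 satisfies the stopping rule. If the value is high, the section says that "the trial is likely to meet its primary outcome even with the reduced sample size". The DSMB uses the result to recommend continuing or stopping. The section names no independent statistician for the calculation.

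Three other places bear on this:

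- **Who will be blinded {17a}** calls the trial unblinded and says the data analysis will not be blinded because study investigators perform it. It then says that certain named people "will, however, be blinded to treatment assignment in conducting their analysis until results are finalized".
- **Primary inferential analyses (Hypothesis 1)** fixes the final test: "Alpha will be set at 0.05 for this planned comparison".
- **Composition of the data monitoring committee {21a}** lists a biostatistician among the DSMB members.

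**The concern.** Conditional power under the observed trend needs outcome data split by arm. Coding the arms would hide the direction but still show the size of the difference. As written, the people who learn the interim result are the people running the trial.

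In this trial they have several ways to act on it, even without intending to:

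- The principal or site investigator approves each participant for randomization (Implementation {16c}), and exclusion may rest on investigator discretion (Eligibility criteria {10}).
- Investigators lead weekly meetings on recruitment, retention and data collection ({5d}).
- Participants who drop out and have no available records are counted as not suppressed (Preliminary analyses and missing data, {20a}). Effort in tracing people and retrieving records therefore feeds directly into the primary endpoint.

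A second, smaller issue is the updated target. The same group proposes it, and nothing says it must be fixed before the effect is seen or may not be changed afterwards.

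The trigger is realistic. Recruitment {15} and the Discussion both anticipate recruitment difficulty, and a third site was added for that reason.

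**Working it through.** **Inputs from the protocol.** Sample size {14}: "power=.80, and *N*=240", three follow-up times, within-person correlation ρ "from 0.10 to 0.80", and a minimum detectable difference of 15 points. Allocation: "The study will begin with 240 participants evenly assigned to the intervention and control groups (80 per city"), so 120 per arm. Alpha is 0.05. Sidedness is not stated; I take it as two-sided, which is 0.025 in the upper tail.

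**Assumptions.** The protocol gives no interim size or information fraction. I use information fractions t = 0.3, 0.5 and 0.7 for the rule as written, and interim sizes of 80, 120 and 160 for the question of target choice.

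**1. The plan's own figure.** For a time-averaged contrast with exchangeable correlation, the design effect is (1 + 2ρ)/3. At ρ = 0.55 this is 0.70, so the effective size is 120/0.70 = 171 per arm. Comparing 50% with 65% at 80% power needs 170 per arm. The stated 15 points therefore reproduces at ρ of about 0.55 (power 0.805). At ρ = 0.8 power is 0.716. So 240 is a sound reference size within the stated range, though not at its upper end.

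**2. The rule as written, with the target fixed before the look.** With interim statistic z₁ at fraction t, conditional power under the current trend is

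CP = 1 − Φ[(1.96 − z₁/√t)/√(1 − t)].

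Hence CP ≥ 0.5 exactly when z₁ ≥ 1.96√t, which is 1.07, 1.39 and 1.64 at t = 0.3, 0.5 and 0.7. Passing that threshold means continuing, not claiming benefit.

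| t | Two-sided error, stop ignored | Upper-tail error, stop obeyed |
|---|---|---|
| 0.3 | 0.050 | 0.015 |
| 0.5 | 0.050 | 0.016 |
| 0.7 | 0.050 | 0.017 |

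There is no inflation in any row.

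**3. The target chosen with knowledge of the effect (not described in the text, but not barred).** For interim size n₁ and final target n, with t = n₁/n, the null probability of a final upper-tail rejection given z₁ is

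CE(n) = 1 − Φ[(1.96 − √t·z₁)/√(1 − t)].

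Example with n₁ = 120:

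- At z₁ = 2.2, a target of 130 gives (1.96 − 0.961 × 2.2)/0.277 = −0.55, so CE = 0.71. A target of 240 gives (1.96 − 0.707 × 2.2)/0.707 = 0.57, so CE = 0.28. A small target helps.
- At z₁ = 0.5, a target of 130 gives CE below 0.0001 and 240 gives 0.012. A large target helps.

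The worst case takes, for every z₁, the target between n₁ + 10 and 240 (steps of 10) with the largest CE, and averages over z₁ ~ N(0,1).

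| Interim n | Stop not binding | Stop binding, same target choice | Stop binding, best target among those passing CP ≥ 0.5 |
|---|---|---|---|
| 80 | 0.039 | 0.025 | 0.029 |
| 120 | 0.037 | 0.024 | 0.028 |
| 160 | 0.034 | 0.023 | 0.026 |

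The reference value is 0.025 throughout.

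**4. Operational bias.** No figure can be derived from the protocol for the effect of the team's knowledge on recruitment, tracing or record retrieval. That part rests on the roles and the endpoint rule set out above.

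**The case against.** **An early stop for efficacy.** A reader might infer that the section permits an unadjusted stop for benefit. Modelling an unadjusted stop at 1.96 gives a two-sided error of 0.083 at half of the information and 0.071 at 80%. The document does not support that reading. Its only rule is for futility, it contains no interim significance test or efficacy boundary, and high conditional power leads on to a reduced target that still has to be reached. Those figures describe a different design.

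**A conflict with the safety section.** A reader might also see a contradiction with Monitoring of safety data by the DSMB: "Unblinded data will not be released to site investigators unless necessary for safety reasons". That sentence concerns site investigators and safety monitoring. The next one allows other unblinded data to reach investigators at the DSMB's request. No contradiction is shown.

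**A conflict with analyst blinding.** Section {17a} states both that analysis is not blinded and that some people will be blinded. Names are removed, so it cannot be told whether those people would run the interim analysis. The fit is uneasy, but it is unclear rather than contradictory.

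**Order of steps.** The target is mentioned before the analysis, is prompted by accrual, and is an input to conditional power. This is a fair reading and makes a data-driven target less likely. It stops short of a requirement, and nothing prevents a later revision.

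**Charter detail.** Closed sessions and the identity of the computing statistician are often left to a DSMB charter, which is not shown. That would answer a silence. Here the protocol itself assigns the calculation to the investigators.

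**Conclusion.** The concern stands in a limited form. The protocol gives investigators both the choice of updated target and an analysis that reveals the interim effect, and it states no separation. In an open-label trial whose primary endpoint depends on tracing and record retrieval, that is an avoidable route to bias. Its size cannot be quantified from the document.

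The type I error issue is secondary and conditional. It needs the target to be set or revised with the effect known. In the worst case, with interim sizes of 80 to 160 and a ceiling of 240, upper-tail error is about 0.034 to 0.039 against 0.025 if the futility stop is not binding. Non-binding is a reasonable reading, because the result only guides a DSMB recommendation. If the stop is binding, the error stays near 0.025, at most 0.029. These are upper limits over the targets considered, not predictions. With the target fixed before the look, the futility analysis needs no alpha adjustment.

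The point should be corrected but does not threaten the design.

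**What to change.** Amend Interim analyses {21b} to state four things:

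1. The updated target is set and documented from accrual information alone, before any outcome is examined by arm.
2. The DSMB biostatistician, already a member, computes conditional power in closed session.
3. Investigators receive only the recommendation to continue or stop, not the effect estimate or the conditional power.
4. The target may not be reduced again after the look.

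The cost is a few sentences in the protocol and DSMB charter and a little work for the DSMB biostatistician. No participants, visits or analyses are added, and the final test stays at 0.05.

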### Methods for additional analyses (e.g., subgroup analyses) {20b}

Data analysis plan and statistical procedures to address mediation and moderation.

#### Moderation analyses

*THR* will buffer the impact of syndemic factors on hypothesized outcomes. The GEE model will be used to examine the relationship between syndemic factors and the hypothesized outcomes (HIV viral suppression, engagement in MOUD, and HCV treatment). Then an interaction between the syndemic factors and treatment assignment will test whether the impact of syndemic factors were lessened in *Tele-Harm Reduction*.

#### Mediation analyses

The impact of *THR* will be mediated through increased engagement and retention in substance use treatment.

To maximize rigor, these analyses will not be performed with classical multiple regression-based mediation techniques such as the Baron and Kenny causal steps approach [55]. Instead, mediation analyses will be conducted using structural equation modeling (SEM) and bootstrapped tests of significance of the product of coefficients (*a***b*, where *a* is the path coefficient from the intervention to mediator, and *b* is the path coefficient from mediator to outcome). We will use M*plus* [56] to perform mediation analyses because it unites SEM with causal inference-based mediation methods in the same analysis platform. Alpha will be set at .05 for all hypothesis tests in these exploratory analyses.

#### Cost and cost-effectiveness analysis

Using a micro-costing approach, detailed information on the costs of each strategy (*THR* and off-site linkage to HIV care) will be collected using tailored version of the standardized costing survey, the Drug Abuse Treatment Cost Analysis Program (DATCAP) [40]. The DATCAP is flexible in that it organizes resources across standard categories: personnel, consultants and contractors, buildings and facilities, equipment, supplies, donated or subsidized resources, and miscellaneous (e.g., licensing fees, administrative/overhead). It electronically generates key economic cost summary statistics using data on intervention engagement and patient case flow: total annual program cost, average annual cost per patient; average cost (per participant) per treatment episode.

### Methods in analysis to handle protocol non-adherence and any statistical methods to handle missing data {20c}

We will address any incomplete data with multiple imputation (MI) [57], which makes the relatively mild assumption that incomplete data arise from a conditionally random (MAR) mechanism [54]. Auxiliary variables will be included to help meet the MAR assumption.

### Plans to give access to the full protocol, participant-level data, and statistical code {31c}

In terms of our data sharing plan, we will provide de-identified data to interested investigators 1 year after publishing the primary outcome paper. After obtaining IRB approvals for planned analyses, and any needed data sharing plans, de-identified data will be sent.

## Oversight and monitoring

### Composition of the coordinating center and trial steering committee {5d}

For this three site proposed project, we have developed an organizational system for the study with well-coordinated data management. The data monitoring and management procedures will be established to maintain active, clear communication at each site and between sites. Specifically, Drs. [name], [name], [name], [name], [name], [name], and [name] will hold weekly zoom meetings with site study staff to direct study activities. This meeting schedule will be maintained throughout all years of the project. These meetings will provide general training and address consistency of procedures as well as problems and challenges. Topics will include issues of recruitment and retention, data collection/management/analysis, budget, and protocol fidelity. Drs. [name], [name], [name], and [name] will supervise and train harm reduction counselors in the *THR* intervention at both sites. [name] will work with [name] to generate regular quality control reports for the sites and make real-time corrections.

The *THR* manual was developed by Drs. [name], [name], [name], [name], [name], and [name] in conjunction with harm reduction counselors. Regular zoom meetings to support harm reduction counselors in the delivery of the intervention will occur. Drs. [name], [name], [name], and [name] will assess the extent to which study intervention was implemented in a manner that is maximally consistent with the intent of the intervention manual though periodic fidelity monitoring of intervention session audio recordings.

Data forms will undergo a rigorous systematic editing process prior to entry into the REDCap database. [name] will routinely evaluate the data and discuss any problems with study staff and investigators at the weekly team meetings. Data management formal reports on record status across the three following domains will be employed: entered, verified, and edited. These reports will be evaluated once monthly during team meeting. To help ensure data protection, backup copies will be automatically generated by our computer systems. Data collected from study assessments and questionnaires will be entered directly into REDCap. Confidentiality is assured as participants will be identified on all study materials only by participant number, visit number, and date of visit. By recording the study data in this manner, the information can be considered “de-identified,” and therefore, compliant with the Standards for Privacy of Individually Identifiable Health Information (“Privacy Rule”) of the Health Insurance Portability Act of 1996 (“HIPAA”).

### Composition of the data monitoring committee, its role and reporting structure {21a}

To fulfill its mission of ensuring the safety and integrity of the study, it is necessary that the Data Safety Monitoring Board (DSMB) be comprised of members who possess a high degree of competence and experience, as well as the ability to function independently of all other parties involved in the study. The DSMB members will function free of the career and financial interests of its members and DSMB consists of three members with experience in conducting clinical intervention research on HIV treatment, expertise in biostatistics, and a thorough knowledge of clinical trial ethics and human subject protection issues. The DSMB chair is [name]. [name] is the harm reductionist. The biostatistician is [name]. [name] will serve as medical monitor.

The DSMB will meet annually by zoom conference and be updated semi-annually by report. At the yearly meeting, members will review randomization data as well as adverse events. The following serious adverse events (SAEs) will be reported within 24 h: deaths, hospitalizations, fatal and non-fatal drug overdose, and psychiatric hospitalizations.

### Adverse event reporting and harms {22}

It is unlikely that participants will be at substantial risk for harm as a result of study participation. They will be prescribed ART and be monitored for potential medication side effects as part of their clinical care outside of specific study labs. Any drug-related toxicities (e.g., elevated creatinine) will be monitored by the study team. Additionally, participants may find some of the questions asked in the questionnaire to be upsetting. Study labs will be conducted routinely and may cause slight discomfort. There is always the potential risk of loss of confidentiality, but procedures are in place to prevent this potential risk. Using telehealth, it is possible that a sign or symptom could be missed. Peers will assist the physician and psychologist in physical diagnosis by taking photos of any wounds and securely emailing them to the clinicians. In-person exams are available at the SSPs. The physician will conduct a thorough review of systems.

We will enroll PWID with HIV initiating ART who will be queried for new potential adverse events at each research visit after screening informed consent. In the THR arm, peer harm reduction counselors will receive training to address medication non-adherence, sexual and injection risk taking, and substance use behaviors. The clinical psychologist will be available on-demand for any participant in either study arm experiencing severe emotional distress, suicidality, or homicidality. He will be backed up by the five study clinicians who have a rotating on-demand call schedule. Additionally, the SSPs have licensed mental health counselors on staff in the case of mental health crisis. During the behavioral assessments, the REDCap survey will automatically indicate provide an alert for a score on the CES-D that suggests that the person is experiencing severe depressive symptoms. Any necessary linkage to emergency services will be provided. With respect to blood draws, each of these procedures will be carried out phlebotomists trained to work with PWID or study physicians to minimize the accidental injury or discomfort to the participants. Participants who experience harm as a result of these procedures will receive first aid from study staff and referral to medical professional if needed.

